formulated by Karachi University (chemistry department laboratories) for 20-30 seconds, thrice daily for 6 days. Group D (n=10) patients will use 2% hypertonic saline (Plabottle® by Otsuka Inc.) gargle and nasal lavage for a similar time period. Group E (n=10) will serve as positive controls. These will be given simple distilled water gargles and nasal lavage for 20-30 seconds, thrice daily for six days. For nasal lavage, a special douche syringe will be provided to each participant. Its use will be thoroughly explained by the data collection officer. After each use, patient is not supposed to eat, drink or mouth rinse for next 30 minutes.

**Discontinuation of intervention {11b}:** Patients who develop rashes, or any other mucosal reaction in oral mucosa or patients who do not wish to continue with the gargles and nasal lavage will be discontinued in the study.

**Compliance on intervention {11c}:** The data collection officer will monitor the amount of gargling solution consumed on daily basis to record the patient compliance on intervention. And once the study is over, the residual bottle will be collected and sent to the incineration. Similarly, any unused/ partially used study drug bottle will be destroyed via incineration.

**Concomitant care {11d}:** Study participants will continue to get their needed routine inpatient medical/pulmonology care concomitantly as per the individual requirements under the care of the attending physician(s).

**Outcomes {12}:** Primary outcome is the reduction in the intra-oral viral load confirmed with real time PCR. Secondary outcome is the change in inflammatory biomarkers (IL-2, IL-4, IL-6, IL-10, TNF- $\alpha$ , IFN- $\gamma$  and IL-17) profiles in the five study groups.

**Participants' timeline {13}:** The timeline has been added as a flow diagram at the end of the protocol. Please see figure 1 on page no. 15.

**Sample Size {14}:** As there is no prior work on this research question, so no assumptions for the sample size calculation could be made. The present study will serve as a pilot trial. We intend to study 50 patients in five study groups. For details, please refer to figure 1 on page no. 15.

**Recruitment {15}:** Patients who are laboratory confirmed COVID-19 within 7 days of the onset of their symptoms who are already admitted as inpatient at the Aga Khan University Hospital, Karachi, Pakistan will be contacted for a voluntarily participation in the study.

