**Retention of study participants {18b}:** To retain maximum number of patients in the study, the data collection officer will keep the contact number of all the recruited patients, so that even if they are discharged from the hospital, they will be encouraged to continue with the study protocol and present to us on the day 7 at the AKUH dedicated COVID-19 testing facility for the collection of their endpoint pharyngeal swabs.

**Data management {19}:** A trained data collection officer will be responsible for data entry, coding, security, and storage. To ensure data quality, double data entry will be followed. The data collection officer will ensure coordination with the investigators and the statistician.

The period of retention of the data will be according to the CTU policy on this subject i.e. 15 years after the completion of the trial. The biological samples (pharyngeal swabs), and the partially consumed study drug will be discarded via incineration immediately after the data collection.

**Data Analysis {20}:** Data will be analyzed using SPSS for Windows (version 23.0 SPSS) and Graph Pad Prism 7.0 software.

Mean and standard deviation of the continuous variables (age, COVID-19 viral counts and cytokine profiles at baseline and endpoint etc.) will be computed. Frequency distribution of the categorical variables will be determined (gender, co-morbidities, presence of hypertension, diabetes, periodontal status etc.) Repeated measures ANOVA will be used to compare the reduction in intra-oral viral load and the changes in the inflammatory biomarkers in the study groups. In case of substantially low count of participants in the study groups, non-parametric tests such as Kruskal-Wallis or Friedman test will be employed. Generalized Estimation Equation (GEE) will be done to predict changes in the COVID-19 viral load and cytokine profiles. A subset analysis using Zero inflated negative binomial (ZINB) model will be employed, provided a

significant reduction in viral load is observed in any of the study groups. A p-value of  $<0.05$  will be taken as statistically significant. {20a}

The **biases and confounders** can be taken care at following four levels:

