At recruitment stage, we will use restriction i.e. only those COVID-19 positive subjects will be recruited who have no other major co-morbidities. At intervention assignment, the random group allocation will ensure even distribution of the confounders in the study groups, thus their differential effect on the outcome will be taken care of. At analysis stage, we will employ GEE regression analysis (as described above) to account for biases and confounders and lastly, the subset analysis will stratify the data and nullify the effect of biases.

Interim analysis {20b} is not planned on account of a short duration of the study. Intention to treat analysis (ITT) will be adopted for missing data and protocol violations or deviations by uncompliant patients. {20c}

**Data monitoring {21a}:** It will be done bimonthly at two levels. The data monitoring committee comprising of principal and co-investigators will be responsible for the monitoring the data at the primary level whereas the CTU at the university level will oversee and monitor the overall conduct of the study.

The decision of termination of the study {21b} will be made in consultation with the director CTU and the sponsors/ funding agency. The decision will be made after mutual consensus of the parties.

**Harms/ adverse reaction reporting {22}:** The adverse events will be documented for each patient and will be reported bimonthly to the clinical trial unit (CTU). This will also documented in the final report. Sponsor/ funders will be notified of the adverse event using their case report. Due to topical nature of the intervention, most likely harm would be an allergic reaction to any of the study drugs [Povidone-Iodine, Hydrogen Peroxide or Neem Extract (*Azadirachta indica*)]. In case of any serious harm, the advice of the primary attending physician will take precedence over others. However, such patient will be discontinued in the trial, CTU and sponsors informed and un-blinding will be followed as prescribed in section 17b. The role of patient's medical insurance will be decided on individual basis

**Study Audit {23}:** CTU reserves the right of carrying out study audit by internal or external auditors anytime.

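### With swabs only on day 1 and day 7, the planned repeated measures ANOVA is a change-score test; it is valid, but adjusting for the baseline viral load already collected would usually be more precise at almost no cost

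*Protocol*

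**What the plan says.** The Outcomes section of the protocol states: "Primary outcome is the reduction in the intra-oral viral load confirmed with real time PCR". The Specimen collection section provides two swabs per patient, one before the first gargle on day 1 and one on day 7.

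For the comparison between groups, the Data Analysis section says: "Repeated measures ANOVA will be used to compare the reduction in intra-oral viral load and the changes in the inflammatory biomarkers". Kruskal-Wallis or Friedman tests are a fallback if group counts turn out very low, with no number attached. It then adds: "Generalized Estimation Equation (GEE) will be done to predict changes in the COVID-19 viral load and cytokine profiles". The paragraph on biases and confounders makes GEE the means of dealing with confounding at the analysis stage. Significance is set at p below 0.05.

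On size, the Sample Size section says "We intend to study 50 patients in five study groups" and explains that "no assumptions for the sample size calculation could be made". Each arm has 10 patients; for the distilled water arm, for example, "Group E (n=10) will serve as positive controls".

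Two further statements stand in the paragraph on biases and confounders. On allocation: "the random group allocation will ensure even distribution of the confounders in the study groups". On recruitment: "only those COVID-19 positive subjects will be recruited who have no other major co-morbidities".

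Baseline viral load is nowhere named as a covariate. For GEE, the protocol gives no variance estimator, working correlation, covariate list or form of test.

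**The concern.** With one baseline and one endpoint, repeated measures ANOVA subtracts the whole baseline value from the day-7 value. That is the best use of the baseline only when the correlation between the two is close to 1. When it is lower, subtraction adds baseline noise to the outcome. A chance baseline difference between arms then also shifts the estimate through regression to the mean: an arm that happens to start higher will appear to fall further. With 10 patients per arm there is little precision to spare, and such imbalances can be large.

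The protocol relies on randomisation to equalise confounders, which it does on average but cannot guarantee in arms of 10. It then relies on GEE, whose usual robust standard errors are large-sample approximations. At stake are the precision of the primary comparison and, depending on how GEE is run, the reliability of its p-values.

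**Working it through.** The protocol states no power, effect size, SD or correlation, so there is no figure of its own to reproduce.

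**Inputs from the protocol:** five arms, 10 patients per arm, two time points, significance level 0.05 (taken as two-sided).

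**Assumptions:** equal SD at both times; baseline to day-7 correlation rho between 0.3 and 0.9; for the power example, SD 1.5 log10 and a true difference of 2 log10 between two arms.

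**1. Variance.** Per patient, in units of SD squared:
- change score: 2(1 − rho)
- ANCOVA residual: 1 − rho² = (1 − rho)(1 + rho)
- ratio, ANCOVA to change score: (1 + rho)/2

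This gives 0.65 at rho 0.3, 0.75 at 0.5, 0.85 at 0.7 and 0.95 at 0.9. Simulation at 10 per arm, which includes the small cost of estimating the slope, gave 0.67, 0.77, 0.87 and 0.97.

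**2. Pairwise power.** The standard error of a difference between two arms is the per-patient SD × √(2/10). The error variance is pooled over all five arms, with 50 − 5 = 45 degrees of freedom for the change score and 50 − 6 = 44 for ANCOVA.

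| rho | SE, change score | SE, ANCOVA | Power, change score | Power, ANCOVA |
|---|---|---|---|---|
| 0.3 | 1.5 × √1.40 × √0.2 = 0.794 | 1.5 × √0.91 × √0.2 = 0.640 | 69% | 86% |
| 0.5 | 1.5 × √1.00 × √0.2 = 0.671 | 1.5 × √0.75 × √0.2 = 0.581 | 83% | 92% |
| 0.7 | 1.5 × √0.60 × √0.2 = 0.520 | 1.5 × √0.51 × √0.2 = 0.479 | 96% | 98% |

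Allowing for estimation of the slope lowers the ANCOVA figures by less than one percentage point.

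**3. Validity.** In 40,000 simulated null trials per setting with normal data, repeated measures ANOVA rejected in 4.9 to 5.2% and ANCOVA in 5.0 to 5.1%. Both hold the nominal level.

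**4. Chance imbalance.** For a baseline SD of 1, 1.5 or 2 log10 (assumed), the probability that at least one of the four active arms differs from the control arm by more than 1 log10 at baseline is 8%, 37% or 63%. Given a baseline difference d, the expected change-score difference is shifted by (1 − rho) × d. For d = 1 log10 this is 0.7 log10 at rho 0.3 and 0.3 log10 at rho 0.7.

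**5. GEE at 10 per arm under no effect.** False-positive rates by version:
- uncorrected robust variance, 4-df omnibus Wald test: 13.6 to 14.1%
- uncorrected robust variance, one pairwise contrast: 7.8 to 8.3%
- n/(n − 1) correction, omnibus: 10.5 to 10.9% with a chi-square reference, 8.4 to 8.8% with an F reference
- bias-reduced robust variance, omnibus chi-square: 8.5%
- pooled model-based variance, omnibus: 6.6 to 6.8%
- uncorrected robust omnibus test on skewed (lognormal) data: 9.5%

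**6. Text comparison.** The paragraph on biases and confounders describes a restriction to patients without major co-morbidities. The eligibility criteria contain no such restriction. The Data Analysis section plans to tabulate co-morbidities, hypertension and diabetes. These three places do not agree.

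**The case against.** The strongest case for the plan is that nothing in the primary test is wrong. The primary outcome is a reduction, a group-by-time test addresses a reduction directly, and under randomisation it is unbiased with a 5% error rate. Chance baseline imbalance is already counted in that error rate. The study is a pilot with no power claim, so lost precision contradicts no stated figure. All of this stands, and it is why the point concerns efficiency. It does not remove the point: the protocol also states comparative efficacy hypotheses and a significance threshold, and the baseline values needed for a sharper comparison are already being collected.

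The size of the gain is also open. It rests on an assumed correlation, and at rho 0.7 or above little is gained. This stands too, so a range is given.

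A reader might infer that the plan commits the trial to a GEE that nearly triples the false-positive rate. The documents do not support that. A rate near 14% needs uncorrected robust standard errors together with a 4-df omnibus Wald test, and the protocol specifies neither. Other versions give roughly 7 to 11%. The variance estimator is commonly settled in a statistical analysis plan. GEE is also not the test named for comparing viral-load reduction between groups. Nor does the protocol rule out adjusting for baseline within GEE, since its covariates are left open.

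The non-parametric fallback means the analysis is not wholly fixed, but as named it has no numeric trigger and makes no baseline adjustment.

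**Conclusion.** The point holds as a recommended improvement. The named analysis of the primary outcome is a change-score test: valid, but usually less precise than ANCOVA. The variance saving is 35%, 25%, 15% and 5% at rho 0.3, 0.5, 0.7 and 0.9. The power gains shown rest further on an assumed SD of 1.5 and effect of 2 log10; none of these values comes from the protocol.

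The GEE concern is a conditional caution: about 8% false positives for one contrast and about 14% for the omnibus test if uncorrected robust standard errors are used. It is not something the protocol states or fixes.

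Two side points rest on the text alone. The claim that randomisation guarantees balance is too strong at 10 per arm, and the co-morbidity restriction does not match the eligibility criteria. Neither makes the primary test invalid.

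**What to change.** - **Primary model:** replace repeated measures ANOVA with ANCOVA of day-7 log10 copies on arm and baseline log10 copies, using t and F reference distributions. Use the same form for each log-transformed cytokine.
- **GEE:** let the ANCOVA replace it, or keep it with a stated small-sample method. A bias-reduced variance with a chi-square reference still gave 8.5%, so the variance correction and the reference distribution should be chosen together and checked at 10 per arm.
- **Allocation wording:** say that randomisation balances confounders on average and that baseline load is adjusted for in the analysis.
- **Co-morbidity restriction:** reconcile the paragraph on biases and confounders with the eligibility criteria and with the planned tabulation of hypertension and diabetes.

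The cost is one residual degree of freedom (45 to 44) and a change of wording. No extra patients, swabs or assays are needed.

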## **MATERIALS & METHODS:**

**Trial design {8}:** It will be a parallel group, quadruple blind-randomized controlled pilot trial annexed with a laboratory based study.

**Study settings & duration {9}:** The clinical trial will be carried out at the Aga Khan University Hospital (AKUH), Karachi, Pakistan. The total duration of the study is expected to be 6 months i.e. August 2020-January 2021. The viral PCR tests will be done at main AKUH clinical laboratories whereas the immunological tests (cytokine analysis) will be done at the Juma research laboratory of AKUH. The study protocol is already registered at [www.clinicaltrials.gov](http://www.clinicaltrials.gov) with ID# NCT 04341688.

**Sampling technique & Eligibility criteria {10}:** Non probability, purposive sampling technique will be followed to identify a total of 50 participants for this study. The inclusion criteria are laboratory confirmed COVID-19 positive males or females (in the age range of 18-65 years), with mild to moderate disease, already admitted in the AKUH. Subjects who have more than 7 days of the onset of COVID-19 symptoms, edentulous patients, subjects with low Glasgow coma score, intubated patients, history of radiotherapy or chemotherapy will be excluded. Patients who are being treated with any form of oral or parenteral antiviral therapy will be excluded. Patients with known pre-existing chronic mucosal lesions such as lichen planus will also be excluded. Patients who are allergic to the study drugs (Povidone-Iodine, Hydrogen Peroxide, Neem Extract or Hypertonic Saline) will also be excluded.

**Intervention {11a}:** Group A (n=10) patients on 10 ml gargle and nasal lavage using 0.2% Povidone-Iodine (Betadiene® by Aviro Health Inc./ Pyodine® by Brooks Pharma Inc.) for 20-30 seconds, thrice daily for 6 days. Group B (n=10) patients will be subjected to 10 ml gargle and nasal lavage using 1% Hydrogen peroxide (HP® by Karachi Chemicals Products Inc./ ActiveOxy® by Boumatic Inc.) for 20-30 seconds, thrice daily for 6 days. Group C will comprised of (n=10) subjects on 10ml gargle and nasal lavage using Neem extract solution (*Azardirachta indica*)

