**Group allocation/ Randomization {16a}:** The assignment to the study group/ allocation will be done using sealed envelope method under the supervision of Clinical Trial Unit (CTU) of Aga Khan University, Karachi, Pakistan. The patients will be randomized to their respective study group immediately after the eligibility assessment and consent administration is done.

**Allocation concealment {16b}:** All the study drugs will be kept in identical dark colored bottles so that the intervention is masked.

**Implementation {16c}:** The Neem extract (*Azadirachta indica*) will be compounded at the Chemistry department, University of Karachi, Pakistan. This will be arranged from there whereas other drugs are stored at AKUH pharmacy/ distribution department. The CTU will ensure that only labels mentioning A, B, C, D or E are pasted on the bottles.

**Blinding/ masking {17a}:** Study will be blinded in quadruple. Patients, intervention provider, outcome assessor and the data collection officer will be blinded. The groups will be labelled as A, B, C, D or E. The codes of the intervention will be kept in lock & key at the CTU and will only be revealed at the end of study or if the study is terminated prematurely.

**Un-blinding {17b}:** Although, un-blinding is not permissible, however, if a participant recognizes the intervention using his/her prior knowledge or experience; they will still be encouraged to continue with the study drug till the end of the study. But if any patients develops a serious reaction to the intervention drug, then un-blinding will be done. The principal investigator will consult CTU and with their permission and taking primary attending physician onboard, un-blinding for the patient in question will be done. This will be documented on the proforma.

**Specimen collection {18a}:** The baseline oral swab will obtained (by a trained data collection officer using the required PPEs) from the posterior pharyngeal wall/ tonsillar area of the study participant on day one before initiating the gargles. Study participants will continue to use the

gargle and nasal lavage for 6 days. The end-point oral-pharyngeal swab will be taken on the day 7. Participants will be provided with a protective hood so that they themselves don't generate aerosols in the immediate vicinity while carrying out the gargling and nasal lavage. For nasal lavage, they will use the special douche syringe as described earlier.

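### The low-count fallback allows a Friedman test that cannot compare the five arms, and the zero-inflated model is run only after a significant fall in any group, with no comparator stated

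*Protocol*

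**What the plan says.** The design is stated under Trial design {8}: "It will be a parallel group, quadruple blind-randomized controlled pilot trial". Sample Size {14} adds "We intend to study 50 patients in five study groups", and Intervention {11a} gives 10 patients per arm, for example "Group D (n=10) patients will use 2% hypertonic saline". Specimen collection {18a} has one baseline swab, from the "study participant on day one before initiating the gargles", and one endpoint swab on day 7, so each patient has two measurements.

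Data Analysis {20} names repeated measures ANOVA as the comparison of viral load reduction and cytokine change between groups. The fallback follows: "In case of substantially low count of participants in the study groups, non-parametric tests such as Kruskal-Wallis or Friedman test will be employed". GEE is also planned. A subset analysis with a ZINB model is conditional: it is run if a "significant reduction in viral load is observed in any of the study groups". The significance level is 0.05. The paragraph on biases and confounders then says that "the subset analysis will stratify the data and nullify the effect of biases".

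**The concern.** The primary objective is to compare agents, so any test that stands in for the ANOVA must compare arms. The fallback offers two tests as though they were interchangeable, and they answer different questions. Kruskal-Wallis on change asks whether the arms differ. Friedman is for related samples and, with two time points, asks only whether load changed over time. The condition for switching carries no number although the planned size is already 10 per arm, so either test could be justified once the trial is under way.

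The gate on the ZINB model raises a similar problem. On its natural reading, a reduction in a group is measured against that group's own baseline, and the distilled-water arm is one of the five groups. Patients enter within 7 days of symptom onset and are swabbed again on day 7, so some fall without any effective gargle is plausible. A change over time that all arms share could then be taken for an effect of the agents, and an analysis selected by that route is credited with removing bias.

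**Working it through.** **Inputs from the protocol.** Five parallel arms of 10, and 5 × 10 = 50, which matches the stated total. Two swabs per patient. Alpha 0.05, sidedness not stated. There is no effect size, SD or power to reproduce: "As there is no prior work on this research question, so no assumptions for the sample size calculation could be made".

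**Assumptions, not in the protocol.** Changes are normal. The natural mean fall is expressed in units of the SD of change and varied from 0 to 1. Tests are two-sided at 0.05.

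**1. Friedman with two time points.** If k of n patients fall, the statistic is (2k − n)²/n on 1 degree of freedom, which is the sign test on change. Arm does not enter the formula. Applied within one arm of 10, k = 8 gives (16 − 10)²/10 = 3.6 (p = 0.058) and k = 9 gives (18 − 10)²/10 = 6.4 (p = 0.011). Either way the result is an uncontrolled before-after test. Using arms as the repeated factor instead would need unrelated patients to be matched into arbitrary blocks.

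Simulation with 5 × 10 patients and 3,000 runs, Friedman taken over all 50, gives these rejection rates:

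| True situation | Friedman on time | Kruskal-Wallis on change | ANOVA group-by-time |
|---|---|---|---|
| Same fall of 0.5 SD in all arms | 82% | 4.5% | 4.9% |
| Same fall of 1 SD in all arms | 100% | 3.9% | 4.5% |
| Arms at -1, -0.5, 0, 0.5, 1 SD | 3% | 98% | 98.5% |

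Friedman rejects when no arm differs and misses real differences that average to zero. Kruskal-Wallis holds its level and finds them.

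**2. The ZINB gate, read as within-arm.** For a paired t-test at n = 10, the chance p that one arm shows a significant fall is P(T > 2.262), where T is non-central t with 9 degrees of freedom and non-centrality d√10 (d is the mean fall divided by the SD of change). The arms are independent, so the chance that at least one of five passes is 1 − (1 − p)⁵.

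| d | One arm, p | At least one of five |
|---|---|---|
| 0 | 0.025 | 1 − 0.975⁵ = 11.9% |
| 0.25 | 0.106 | 43% |
| 0.5 | 0.293 | 82% |
| 0.75 | 0.562 | 98% |
| 1 | 0.803 | 99.97% |

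With 6 evaluable patients per arm the last column is 60% at 0.5 SD and 97% at 1 SD. In every row the arms are identical. A gate on the group-by-time term would open in about 5% of such trials whatever the common fall.

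**3. The bias claim.** Whether the gate opens depends on the outcome data and, on this reading, not on a comparison with control. Running a model only after a significant result adds selection. It cannot cancel bias.

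**The case against.** **The fallback sentence already contains a valid test.** Kruskal-Wallis is named first and can compare arms on change. The two tests can also be read as counterparts of the between-group and within-time parts of the ANOVA, and GEE is planned in any case. This stands to the extent that the fallback is not wholly unusable. It does not rescue the wording, which lets either test replace the comparison of arms.

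**The switch depends on numbers of patients, not on outcomes.** Discontinuation and discharge before day 7 can take the evaluable count below 10, so a trigger is not meaningless, and a numerical cut-off may sit in an analysis plan not shown here. That is fair. The absent number is a lesser matter; it counts because one of the two tests it can lead to does not compare arms.

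**The gate could mean a between-group result.** No comparator is stated, and the same paragraph speaks of comparing reductions across groups. So the within-arm reading is the natural one but not a certain one.

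Some stronger readings are tempting, and the documents do not support them:

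- A reader might infer that natural clearance will almost always open the gate. That needs a fall of about 0.75 SD or more, and the protocol gives no clearance figure.
- A reader might infer that every arm, water included, would pass. At 1 SD all five pass in 0.803⁵ = 33% of trials; at 0.5 SD in 0.293⁵ = 0.2%.
- A reader might quote a very small Friedman p-value, such as (80 − 50)²/50 = 18 for 40 of 50 patients falling. Pooling all 50 patients is not stated in the plan, and the fallback is meant for low counts.
- A reader might infer that results beyond the Ct 35 cut-off are modelled as structural zeros. The laboratory section does not say how they are coded, and preferring another model to ZINB is largely a matter of choice.

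Opening the gate only runs a further model in a pilot with no power claim; it does not in itself declare efficacy.

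**Conclusion.** Wrong as written, of moderate severity. That Friedman cannot compare independent arms follows from the parallel design and the two swabs, and needs no assumption about clearance; only its rejection rates do (100% at a common 1 SD fall, 3% when arms truly differ). The gate's size rests on the within-arm reading, a paired t-test at 10 per arm, and assumed natural falls: 11.9% with no true change, and 43% to over 99.9% for falls of 0.25 to 1 SD. On that reading, passing the gate says nothing about one gargle against another or against water, and the claim that the resulting analysis removes bias has no basis. The planned ANOVA and Kruskal-Wallis remain sound routes to a comparison of arms, which is why this is not a more serious fault.

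**What to change.** In Data Analysis {20}:

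1. Remove Friedman as a test for comparing arms.
2. Name Kruskal-Wallis on log10 change from day 1 to day 7 as the single non-parametric comparison of arms. Run it in all cases beside the planned repeated measures ANOVA, whose group-by-time term should be named as the comparison of interest. Drop the switch on patient count.
3. Run the follow-up model unconditionally, or make it conditional on a between-arm result against distilled water.
4. In the paragraph on biases and confounders, delete the statement that the subset analysis nullifies bias.

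The cost is a change of wording and slightly more analysis work. No patient, visit or assay is affected. For scale, Kruskal-Wallis at 10 per arm has about 50% power when one arm falls 1 SD more than the other four (ANOVA about 56%), so the change gives a valid comparison and not a powerful one.

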**Informed consent {32}:** Informed consent will be obtained in Urdu (or in English for those who are well versed with the latter) language where the harms and benefits of the gargles and nasal lavage will be explained along with the method of their use in a simple language. The details are stated in the Urdu and English consent forms. The signed consent forms will be retained for the record purpose.

**Laboratory phase for Biological specimen {33}:** Swabs taken from the posterior pharyngeal wall and tonsillar area will be delivered to the laboratory in the transport medium within 4 hours of the specimen collection. The RNA will be extracted in the biosafety cabinet in the BSL-3 laboratory using QIAamp Viral RNA Mini Kit (Qiagen Inc.). Viral RNA will be used as a template in PCR containing following two sets of CDC approved primers and probes targeting COVID-19 virus and Fast Virus 1-Step Master Mix (Thermofisher Inc.). 2019-nCoV\_NI-F (GACCCCAAAATCAGCGAAAT), 2019-nCoV\_NI-R (TCTGGTTACTGCCAGTTGA ATCTG), 2019-nCoV\_NI-P (FAM-ACCCCGCATTACGTTTGGTGGACC-BHQ1) 2019-nCoV\_N2-F (TTACAAACATTGGCCGCAAA) 2019-nCoV\_N2-R (GCGCGACATTCCGAAGAA), 2019-nCoV\_N2-P FAM-(ACAATTTGCCCCCAGCGCTTCAG-BHQ1). To generate standard curve, we will design a synthetic oligo which will contain target sites for the aforementioned forward & reverse primers and probes. We will clone this synthetic oilgo in pGEMT vector after amplifying it through PCR; calculate its copy numbers and use its different dilutions to generate the standard-curve in PCR. Sample Ct values below 35 cycles will be considered as positive. The unknown sample's Ct values will be plotted on standard curve to know the copy numbers.

Cytokine analyses from the collected specimen will be carried out using Cytometric Bead Array (BD Biosciences) on FACS Celesta analyzer. Cytokine bead array detects cytokines using fluorescence labelled beads coated with antibodies. Following incubation of samples with cytokines, a fluorescence labelled antibody is used for the signal detection. The Median Fluorescence Intensity (MFI) is proportional to the amount of analyte present in the sample. All

procedure will be carried as per manufacturer's instructions. Unknown concentration of cytokines will be quantified through a known standards curve of cytokines. Flow JO software will be used for the final analyses.

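### The zero-inflated negative binomial model named for viral load does not suit PCR copy numbers: if it is run to compare arms of 10, its p-values reject far above 5% when the arms are identical

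*Protocol*

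**What the plan says.** Protocol, Data Analysis {20}, gives the comparison of viral-load reduction between groups to repeated measures ANOVA. Kruskal-Wallis or Friedman replaces it if the groups are very small, and GEE is added. It then says: "A subset analysis using Zero inflated negative binomial (ZINB) model will be employed, provided a". The sentence goes on to state the condition for running the model, namely that a "significant reduction in viral load is observed in any of the study groups". One significance rule, p<0.05, covers all of this.

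The outcome is defined under Laboratory phase for Biological specimen {33}: "The unknown sample's Ct values will be plotted on standard curve to know the copy numbers". The cut-off is also there: "Sample Ct values below 35 cycles will be considered as positive".

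On size, Sample Size {14} says: "We intend to study 50 patients in five study groups". Intervention {11a} puts 10 in each arm.

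The paragraph on biases and confounders adds that "the subset analysis will stratify the data and nullify the effect of biases". It does not say which contrast, time point or covariates ZINB would have.

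**The concern.** ZINB tests take their standard errors from a specific model: integer counts with gamma-Poisson variation within an arm, plus excess zeros. A copy number back-calculated from a Ct is a concentration. Its natural scale is logarithmic, and it can differ between patients by orders of magnitude. With 10 per arm, one or two patients can then set the arm mean, and the model's standard error for the log mean ratio is too small. The test can reject because the distribution is wrong, with no difference between arms.

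At stake is a significant result for one gargle over another that carries no evidence. The section on why the study is important would use a positive finding to support routine pre-procedure rinsing.

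**Working it through.** **Inputs from the protocol.** Five arms, 50/5 = 10 patients each; threshold 0.05 (taken as two-sided); copy numbers from a standard curve; positive if Ct is below 35. The protocol gives no power or error-rate figure, so there is none to reproduce.

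**Assumed, because the protocol gives no value.** Log-normal loads with log10 SD *s* from 0.5 to 2; zeros either random or from a cut-off of 100 copies.

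**Step 1: why the standard error is too small.** A negative binomial has variance μ + μ²/k, so for large μ the squared coefficient of variation (CV²) is about 1/k. A log-normal has CV² = exp[(s·ln 10)²] − 1. Compare this with the median k fitted to simulated log-normal data without zeros:

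- s = 0.5: true CV² = exp(1.151²) − 1 = 2.76; fitted k = 1.07, so 1/k = 0.93.
- s = 1: true CV² = exp(2.303²) − 1 ≈ 200; fitted k = 0.37, so 1/k = 2.7.

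The fitted model sees only part of the real variation.

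**Step 2: two identical arms of 10, nominal 5%.** Rejection rates (%), likelihood ratio / Wald:

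| log10 SD | Arm also in zero part, cut-off zeros | Constant zero part, 30% random zeros | Constant zero part, cut-off zeros |
|---|---|---|---|
| 0.5 | not run | 17 / 21 | 16–18 / 19–21 |
| 0.7 | 27 / 31 | not run | 26–28 / 27–30 |
| 1.0 | 34–38 / 38–43 | 27 / 33 | 32–34 / 32–38 |
| 1.5 | 48–50 / 56 | 32 / 40 | 37–41 / 45–48 |
| 2.0 | 54 / 63 | 34 / 45 | 41–45 / 52 |

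Runs per cell were 200 to 800, so the Monte Carlo standard error is at most √(0.5 × 0.5/200) = 3.5 points. The whole range is 16–63%, or 16/5 = 3.2 to 63/5 = 12.6 times nominal. Sandwich standard errors gave about 15–59%. With five arms, the 4-df likelihood-ratio test rejected in 29–86%.

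**Step 3: how much is misspecification.** On data that truly follow a ZINB, five arms of 10, the likelihood-ratio test rejected in 7–8% and the 4-df Wald test in 13–19%. Part of the excess is therefore small-sample error, but most of the likelihood-ratio excess comes from the wrong distribution.

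**Step 4: alternatives under the same kind of null.** Mann-Whitney, two arms: 2.5–5.5%. Kruskal-Wallis on change, five arms: 5.0–6.8%. ANOVA on change in log10 copies, five arms: 5.2–7.0%.

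**Step 5: the condition for running ZINB.** Five identical arms, baseline around 10^5 copies, within-patient correlation 0.5, natural decline of 1 or 2 log10, SD 0.5–1.5 (all assumed), 400 trials per scenario. Share of null trials in which the condition is met and the five-arm ZINB likelihood-ratio test also rejects:

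- Condition read as a between-group difference: about 6% or less.
- Read as a within-group reduction tested on raw copies: met in 11–100% of trials, joint rate 9–48%.
- Read as a within-group reduction tested on log10 copies: met in 95–100%, joint rate 30–77%.

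**The case against.** A reader might infer that the trial as planned would report false arm differences at the rates in Step 2. The documents do not support that. Those rates apply once ZINB is run, and the protocol runs it only after a significant reduction. If that means a between-group difference, the joint rate is about 6% or less. The wording, which speaks of a reduction in any of the groups, fits a within-group reading at least as well, but the protocol does not settle it.

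A reader might also infer that the main efficacy comparison is invalid. It does not depend on ZINB: ANOVA, the rank tests and GEE carry it, and the study is a declared pilot. Nor does the protocol say that ZINB compares arms. It calls it a subset analysis and says the subset analysis will stratify the data. The contrast tested above is an assumption, and the figures move with the specification, as the table shows. Such details may properly sit in an analysis plan that is not at hand.

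These points limit the size and reach of the concern. They do not remove it. The model itself is fixed in the protocol, for an outcome that the protocol defines as a copy number, under the same 0.05 rule. No specification tried brought the two-arm likelihood-ratio or Wald rate below 16%, and sandwich errors did not help.

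The claim that the subset analysis nullifies bias is a separate overstatement. The simulation does not bear on it.

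**Conclusion.** The concern holds in a conditional form. ZINB is poorly suited to these copy numbers, and if used to compare arms of 10 its p-values cannot be taken at face value. With two identical arms it rejects in about 16–63% of comparisons, given log-normal loads with log10 SD 0.5–2. How many null trials would be affected depends on an unlocking condition that the protocol leaves open: about 6% or less on a between-group reading, about 9–77% on a within-group one, with the decline and correlation assumed in Step 5. This is a defect in a conditional secondary analysis, worth correcting because a named alternative keeps the error near 5%.

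**What to change.** In {20a}, replace the ZINB model with one of two analyses of day-7 viral load by arm:

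- a rank test with values at Ct 35 or above tied at the lowest rank; or
- a model for log10 copies with those values treated as left-censored.

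Report the proportion at Ct 35 or above in each arm separately, with an exact test. If ZINB is kept, use it for description only or take its p-values from permuting the arm labels.

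The rank tests and log10-scale ANOVA were simulated. The censored model was not, so its size at 10 per arm should be checked before it is adopted.

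The cost is a change of wording, with no new data. The count-model rate ratio is lost, and fewer results will reach p<0.05.
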